**13.2 Secondary validity measure: immunochemical markers on tissue examination**

- Pro-inflammatory cytokine (IL-6) / Anti-inflammatory cytokine (IL-10) ratio was obtained and the progression to the proliferative phase was analyzed by comparing the control and experimental groups after 0 and 4 weeks.
- Immunochemical markers are measured in a laboratory by a researcher through RNA sequencing, with final confirmation by the Principal Investigator.

## **14 Criteria for evaluating safety, including adverse events · Methods of evaluation and reporting**

### **14.1 Definition of an adverse event, adverse reaction**

#### **14.1.1 Anomalies**

- **"Adverse Event (AE)"** means any unintended condition, symptom, or disease that occurs in a subject during a clinical trial, including abnormalities in laboratory test results, that is not necessarily causally related to the investigational medical device.

#### **14.1.2 Medical Device Adverse Events**

- **"Adverse Device Effect (ADE)"** means any harmful, unintended reaction caused by an investigational medical device that cannot be causally linked to the investigational medical device.

#### **14.1.3 Serious adverse events, medical device adverse events**

- **"Serious AE, ADE" means an** adverse event or medical device event caused by a medical device used in a clinical trial that meets any of the following criteria

Death or danger to life

You need to be hospitalized or have an extended hospital stay.

Resulted in permanent or significant disability and impairment.

The fetus has malformations or abnormalities.

#### **14.1.4 Unexpected Medical Device Adverse Events**

- **"Unexpected Adverse Device Effect"** means a difference in the appearance or severity of a medical device **adverse event** in light of available information about the medical device, such as a clinical investigator's data sheet or medical device supplement.

### **14.2 Evaluating adverse events**

- If an adverse event occurs, it should be reported using the following severity scale

### **14.3 Causality with clinical devices**

- The relevance of the adverse event to the investigational device is assessed by the investigator by the following criteria and described in the investigator's opinion.

#### **A. Definitely related.**

- (1) There is a discrepancy in the temporal sequence of investigational use and adverse event occurrence.

The adverse event is most likely explained by the use of the investigational clinical device rather than any other reason.

- ③ The adverse event disappears with discontinuation.

- ④ Reuse (only performed if reuse is available) If the result is positive.

The adverse event is consistent with information already known about the clinical device or its class of medical devices.

#### **B. Probably related**

There is evidence that the clinical device was used.

The temporal sequence of the use of the clinical device and the onset of the adverse event is reasonable.

The adverse event is more likely to be explained by the use of the clinical device than by other causes.

U

#### **c. Probably related**

There is evidence that the clinical device was used.

The temporal sequence of the use of the clinical device and the onset of the adverse event is reasonable.

The adverse event is believed to be attributable to the use of the investigational clinical device to the same extent as other possible causes.

④ The adverse event resolves with discontinuation of use of the clinical device (if implemented).

**d. Probably not related**

There is evidence that the clinical device was used.

The clinical device discontinuation result is negative or ambiguous.

Clinical device reuse results are negative or ambiguous.

**d. Definitely not related**

No clinical devices were used on the subject.

The temporal sequence between the use of the clinical device and the discovery of the adverse event is not plausible, and there is an apparent circle of causation for the adverse event.

**BAR. Unevaluable (Unknown)**

Information is insufficient or conflicting to make a judgment, and cannot be supplemented or verified.

**14.4 Evaluation Criteria**

- Subject's complaints of adverse events that occurred during or after use of the medical device: whether there were symptoms of irritation in the hip area (burning, hives, inflammation, itching, pain, etc.)
- Medical examination: presence of skin lesions (erythema, edema, etc.) in the hip area
- Follow-up period: Follow-up will be conducted until 6 months after the end of the study.
- Mild

Evaluate the extent of the medical findings and their causal relationship to the clinical device if they do not interfere with the subject's normal daily life, cause minimal discomfort and are easily tolerated by the subject, the treatment is testimonial and complete recovery does not affect the validity of the medical device.

- Severe (moderate)

If it causes discomfort that significantly interferes with the subject's normal daily life, is reversible with continued treatment, and does not affect the validity of the investigational medical device, the degree of medical diagnosis and the causal relationship to the

investigational medical device will be evaluated.

- severe

Evaluate the validity of the medical opinion and its causal relationship to the investigational clinical device if it prevents the subject from performing normal activities of daily living, is incurable, and if the investigational clinical device affects validity.

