### 9.2 Clinical Trial Methods

#### 9.2.1 Prepare subjects

- The principal investigator selects appropriate subjects who meet the subject selection criteria and who voluntarily agree to participate in the trial.
- Explain to subjects the purpose and methods of the study, the safety and effectiveness of the investigational device, and the methods of investigation.
- Completed informed consent forms for clinical research.
- Describe any side effects that may occur after the trial.

- Determine whether adverse events occurred periodically during the follow-up period.

When applying a medical device, the following procedures are implemented

1) Before applying the device, disinfect the area with a sterile cotton pad soaked in saline solution.

2) Medical Device Applications (25 minutes)

\*Medical device application details

<Subjects will be irradiated for a maximum time (25 minutes) with 4 wavelengths of LEDs at 5 levels of maximum power [level 1 (12 mW/cm^2), level 2 (27.9 mW/cm^2), level 3 (44.6 mW/cm^2), level 4 (61 mW/cm^2), level 5 (90 mW/cm^2)] at a distance of 15 cm from the pressure ulcer on the hip area. LED irradiation is performed 3 times per week>.

3) After applying the device, disinfect the affected area with a disinfectant swab soaked in saline solution.

4) Apply an antibacterial ointment (Silmazin, Bactroban, Repigel, etc.).

5) Dress the wound using a medform.

After one week of treatment, we will perform an otologic examination and examination of the affected area. This will be done for a total of 4 weeks.

Efficacy will be assessed using wound size and degree of re-epithelialization as primary measures and immunochemical markers on biopsy as secondary measures. Safety will be assessed by physical examination and vital signs, as well as adverse event investigation.

Antibiotic therapy and wound disinfection, which are routinely performed in the conservative treatment of pressure ulcers, will be administered as standard, with the addition of light therapy for those participating in the trial. The light is a combination of four wavelengths and is predicted to be beneficial for bactericidal (BLUE wavelength) and tissue regeneration (AMBER and RED wavelengths).

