| Recheck selection criteria/exclusion criteria                      |                       | 
(D1 Advance            |                       |                       |                       |                       |                       |
| Suitability determination and subject identification numbers Grant |                       | 
(Proceed with D1 only  |                       |                       |                       |                       |                       |
| Investigating adverse events                                       |                       |                            |  |  |  |  |                       |

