#### **10.3.5 Visit 15 (D210 ± 2 days)**

Medical examination and measurement of vital signs.

Measurement of erythema, Braden scale, and NRS.

Performed mycobacterial culture and histologic examination.

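### No adverse event check is scheduled at the 6-month visit although 6-month follow-up is promised, and the device-effect and causality wording contradicts itself

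*Protocol*

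**What the plan says.** **Follow-up.** Under the safety criteria in Protocol 14.4: "Follow-up will be conducted until 6 months after the end of the study". Among the study procedures in 9.2.1: "Determine whether adverse events occurred periodically during the follow-up period". Section 10.2 describes how events are found: subjects are taught to report them, and the investigator confirms them by questioning.

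**Schedule.** In the 10.1 table, the row "Investigating adverse events" is marked for Weeks 1 to 4 and for Visit 14 (D29). The Visit 15 (D210) cell is empty, as it is in the row for medical history and drugs. Section 10.3.5 lists examination, vital signs, erythema, Braden scale and pain score for Visit 15, and ends with "Performed mycobacterial culture and histologic examination". It has no line for adverse events, history or medication.

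**Definitions.** Section 14.1.2 describes an adverse device effect as a harmful, "unintended reaction caused by an investigational medical device that cannot be causally linked to the investigational medical device". In 14.3 A, the first criterion for the highest grade is "There is a discrepancy in the temporal sequence of investigational use and adverse event occurrence". Grade c is headed "Probably related", the same label as grade B.

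**The concern.** Safety is in the study title and is the secondary objective (5.1). Section 14.5 compares the severity, type and incidence of adverse events between groups. If nobody is asked about events after D29, an event that begins and resolves before D210 enters the record only if the subject volunteers it. Where the D29 punch biopsy is taken, no questioning about its complications is scheduled afterwards. Without a medication check, the investigator at D210 also lacks a scheduled source for the suspected other drug or treatment that 10.2 wants recorded with each event.

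The causality wording matters because 14.6 requires causality to be determined from these criteria, 14.7 foresees a comparison of device-associated events between groups, and section 17 makes the sponsor's payment for treatment depend on the attribution.

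**Working it through.** **1. Scheduled checks, table against text**

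| Visit | Day | Adverse events, 10.1 | Adverse events, 10.3 | History and medication, 10.1 | History and medication, 10.3 |
|---|---|---|---|---|---|
| 2 | D1 | yes | yes (10.3.2) | yes | yes |
| 3–13 | D3–D26 | yes | yes (10.3.3) | yes | yes |
| 14 | D29 | yes | yes (10.3.4) | yes | yes |
| 15 | D210 | no | no (10.3.5) | no | no |

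Table and text agree on the omission, so a damaged table does not explain it. Both conflict with 9.2.1 and 14.4.

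**2. Is Visit 15 the promised 6-month point?** Taking 30.4375 days per month:
- From the last weekly treatment visit: 210 − 26 = 184 days; 184 / 30.4375 = 6.0 months.
- From Visit 14: 210 − 29 = 181 days; 181 / 30.4375 = 5.9 months.

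Both starting points are shown because 10.1 marks device application at Visit 14 while 10.3.4 does not list it. Either way Visit 15 fits 6 months after treatment. Taken literally, six months after the end of the study would run beyond Visit 15, where no visit exists at all.

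**3. Length of the gap**
- Last scheduled check D29, last visit D210: 210 − 29 = 181 days.
- With the ±2-day windows: from 208 − 31 = 177 to 212 − 27 = 185 days.
- Share of the D1–D210 span: 181 / (210 − 1) = 181 / 209 = 87%. Counted from D0: 181 / 210 = 86%.

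**4. Definition in 14.1.2.** It sets two conditions: the device caused the reaction, and the reaction cannot be causally linked to the device. No event meets both.

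**5. Causality grades in 14.3**

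| Grade | Timing criterion | Weight against other causes |
|---|---|---|
| A, definitely related | a discrepancy | device most likely |
| B, probably related | reasonable | device more likely |
| c, probably related | reasonable | device equally likely |
| d, definitely not related | not plausible | an apparent other cause |

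On timing, the highest grade therefore sides with the lowest and against the two beside it. An event in reasonable time order fails A(1). Grades B and c differ in criteria but not in name, so a record that carries only the label cannot be resolved. The letter d also heads two grades (probably not and definitely not related).

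**The case against.** **Passive capture exists.** A reader might infer that adverse events are not collected at all after D29. The protocol does not support that. Section 10.2 requires a medical examination at each visit and sends findings that meet the definition to the adverse event record; Visit 15 includes that examination, plus a pain score, culture and histology. Recurrence or infection present on D210 can be seen. Spontaneous reports are invited, and 12.3 adds questionnaires or calls for dropouts. This stands, and it limits the point to the missing scheduled questioning. It does not recover events that resolved unreported before D210.

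**The safety objective is set at 4 weeks.** Section 5.1 assesses safety before application and 4 weeks after it, so the omission could be intended. In that case 9.2.1 and 14.4 are the sections out of line; the conflict remains.

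**Translation.** The text is evidently translated, and 14.1.2 and 14.3 may have been sound in the source language. That is likely, but investigators using this text would apply what it says. Grades B and c can also be told apart by letter and criteria, so the shared label is a risk rather than a certain error. The main comparison in 14.5 does not use relatedness.

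**Serious events.** A reader might also infer from 14.1.3, which speaks of an "adverse event or medical device event caused by a medical device used in a clinical trial", that deaths judged unrelated are not serious adverse events, and might size this with the 18% mortality (45 of 250) in 7.3.2. That does not follow. The causal phrase can attach to the device event alone, 14.1.1 defines adverse events regardless of cause, and 14.7 requires all serious adverse events to be notified to the sponsor. The 18% comes from one physician's patients, is linked there to moderate and severe ulcers, and is expected to be lower here. It does not measure this point.

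**Conclusion.** The point holds as an internal inconsistency in safety ascertainment. No adverse event questioning and no medication check are scheduled at D210, although 9.2.1 and 14.4 promise follow-up that only this visit can deliver. The gap is 181 days (177 to 185 with the visit windows), about 87% of the D1–D210 span. This counts days after the last scheduled check, not days on which no event could be recorded. It assumes that the end of the study in 14.4 means the end of treatment, which the day count supports.

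The wording of 14.1.2, 14.3 A(1) and the shared label in 14.3 is wrong as it stands. That events would be misclassified is a consequence of literal use, which the document cannot show, and no rate can be put on it. Nothing here changes the sample size (19 per group, 38 in total) or power. The passages should be corrected, because the safety comparison and the causality record depend on them.

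**What to change.** 1. Add an adverse event check and a history and medication check to Visit 15 in both 10.1 and 10.3.5, worded to cover the whole interval since Visit 14. State that the 6 months in 14.4 run from the end of treatment, and align the 4-week safety objective in 5.1 with this.
2. Reword 14.1.2 to reactions for which a causal link to the device cannot be ruled out.
3. Reword 14.3 A(1) to require a reasonable time order, as B and c already do.
4. Give grades B and c distinct labels, for example probably related and possibly related, and give each grade its own letter. Carry the labels into the case record.

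The cost is a protocol amendment, matching case record wording and a few minutes at a visit that already takes place. One limit remains: a check at Visit 15 cannot cover complications of a biopsy taken at that same visit.

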### **11 Possible side effects and precautions for use**

#### **11.1 Possible side effects**

- Possible side effects include increased exudate, bacterial growth, wound bleeding, and tissue necrosis due to stimulation of the inflammatory response.
- A 2014 Cochrane review by Chen C. et al. found that photobiologic therapy can also cause side effects such as pain, microbleeds, and redness.
- If you have an adverse event, record the name of the event and the severity of the symptoms in the case log.

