#### **14.5 Evaluation Methods**

- Perform analyses on adverse events reported by subjects or identified by secondary review to assess the severity and type of adverse events and the incidence of adverse events in the study and control groups.

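### The severity grades in Section 14.4 combine intensity, reversibility and effect on efficacy, so 9 of 12 attribute combinations have no grade and severity cannot be assigned consistently

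*Protocol*

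**What the plan says.** Section 14.2 states that when an adverse event occurs "it should be reported using the following severity scale". No scale follows in that section. The general definitions of mild, moderate and severe are in Section 14.4:

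- **Mild** covers findings where "they do not interfere with the subject's normal daily life, cause minimal discomfort and are easily tolerated by the subject", and adds that "complete recovery does not affect the validity of the medical device".
- **Moderate** covers an event that "causes discomfort that significantly interferes with the subject's normal daily life". A second condition applies at the same time, namely that the event "is reversible with continued treatment, and does not affect the validity of the investigational medical device".
- **Severe** applies "if it prevents the subject from performing normal activities of daily living, is incurable, and if the investigational clinical device affects validity".

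In this translation 'validity' stands for efficacy. The table of contents lists a primary validity scale where Section 13.1 is headed primary efficacy measures, and Section 13.2 calls its own outcome a validity measure.

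The grades are used. Section 14.5 plans analyses to "assess the severity and type of adverse events and the incidence of adverse events in the study and control groups", and Section 14.6 has mild, moderate or severe entered on the adverse-event record. Among the expected side effects, Section 11.1 lists "increased exudate, bacterial growth, wound bleeding, and tissue necrosis due to stimulation of the inflammatory response", followed by pain, microbleeds and redness.

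**The concern.** Severity normally describes how intense an event is. Whether it resolves is an outcome, and whether it changes wound healing is an efficacy finding. Section 14.4 requires all three to line up before a grade applies, and it gives no rule for an event that meets conditions from different grades. The investigator must then leave the event ungraded or decide which condition to ignore.

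Two kinds of event matter most here. A disabling event that is cured cannot be called severe. A treatable harm in the study ulcer that slows healing is excluded from mild and moderate by its effect on efficacy, and from severe because it is curable. The ulcer also carries the primary measures, wound size and re-epithelialization. The scale can therefore fail for harms that the protocol itself predicts, and it makes a safety grade depend on the efficacy result. With 19 subjects per arm (Section 7.3), a few events graded by different private rules could change the severity summary.

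**Working it through.** Section 14 contains no figure to reproduce. The check is a full enumeration of the definitions.

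**Inputs (all from Section 14.4).** Intensity has three levels: minimal, significant interference, prevents daily activities. Reversibility has two: reversible, incurable. Effect on efficacy has two: no, yes. That makes 3 x 2 x 2 = 12 combinations. A combination has a grade only if it meets every condition of that grade.

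| Intensity | Reversible, no effect | Reversible, effect | Incurable, no effect | Incurable, effect |
|---|---|---|---|---|
| Minimal | Mild | none | none | none |
| Significant | Moderate | none | none | none |
| Prevents daily activities | none | none | none | Severe |

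Graded: 3. Ungraded: 12 - 3 = 9 (75% of combinations).

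**Partial interference.** Mild needs no interference and moderate needs significant interference. Adding a level for some, but not significant, interference gives 4 x 2 x 2 = 16 combinations, of which 16 - 3 = 13 have no grade.

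**Does the result hang on the awkwardly translated clauses?**

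- If the recovery and 'validity' clause under mild is ignored, all four minimal-intensity combinations are mild. Graded: 4 + 1 + 1 = 6. Ungraded: 12 - 6 = 6.
- If every 'validity' condition is ignored, there are 3 x 2 = 6 combinations. Three are graded (minimal and reversible, significant and reversible, preventing daily activities and incurable) and three are not. The disabling but curable event is among the three without a grade.

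**From combinations to events.** The protocol gives no event rates, so the following is assumption only. Let m be the share of events of minimal or significant intensity, q the share incurable and p the share affecting efficacy, all independent. Then

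ungraded share = 1 - [m(1 - q)(1 - p) + (1 - m)qp].

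- m = 0.95, q = 0.05: 0.0975 + 0.90p. At p = 0.10 this is 0.188.
- m = 0.80, q = 0.20: 0.36 + 0.60p. At p = 0.70 this is 0.78.

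Over these settings the ungraded share runs from about 19% to 78%. It reaches 50% at p = (0.50 - 0.36)/0.60 = 0.23 in the second case and at p = (0.50 - 0.0975)/0.90 = 0.45 in the first.

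**After the fix.** With grades defined on intensity alone, 0 of the 12 combinations are ungraded. Partial interference still needs wording.

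**The case against.** The strongest objection is that exact logic is being applied to a damaged translation. The mild definition is hard to read, the severe definition literally says that the device affects 'validity', and the bracketed label on the middle grade is a translation slip: Section 14.6 plainly lists mild, moderate and severe. The label is not counted here. But reversibility and 'validity' recur in all three grades, so the three-part structure is not one garbled phrase, and dropping the unclear clauses still leaves gaps.

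A second objection is that 14.2 does not name 14.4, and a scale may have stood under 14.2 that is not visible in the text. That is possible. The definitions in 14.4 are the only general ones that can be read, and they would conflict with any other scale unless reconciled.

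Third, other safety information remains. Seriousness (Section 14.1.3), causality, type and incidence do not use these grades. Section 10.2 scores erythema, urticaria and blisters from 0 to 3. This limits the damage and stands, but the 0 to 3 scores do not cover exudate, bacterial growth, bleeding or necrosis.

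Fourth, a reader might infer that most events, or all the harms named in 11.1, cannot be graded. The documents do not support this. Nine of 12 counts combinations, not events. Pain, redness or microbleeds that resolve without altering healing fit mild, or moderate if they significantly interfere with daily life. The ulcer harms lose those grades only if they affect healing or do not resolve. Nor would a cured, life-threatening infection that prevents daily activities be capped at moderate: it has no grade, and it is still captured as serious.

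**Conclusion.** The point holds. As written, 9 of 12 attribute combinations have no grade, a curable event cannot be severe, and a treatable event at the ulcer that slows healing fits nowhere. Severity cannot be assigned consistently and depends partly on the efficacy outcome, so the severity summary planned in 14.5 is unreliable.

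It would go too far to call the safety comparison invalid. Incidence, type, causality and seriousness stand apart from this scale, and 14.5 names the two groups alongside incidence, so a comparison of severity between arms is a fair reading but is not spelled out. The number of events affected is unknown; the 19% to 78% range only shows how strongly it depends on assumed shares.

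The conclusion assumes that 'validity' means efficacy, that the conditions within a grade apply jointly, and that 14.4 is the scale 14.2 intends. The finding on disabling but curable events does not need the first assumption.

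**What to change.** In 14.4, define mild, moderate and severe by intensity alone, as the degree of interference with the subject's usual daily life. Word the boundary between mild and moderate so that partial interference falls in one of them. Delete the curability and 'validity' conditions, and make 14.2 refer explicitly to this scale. Keep outcome and effect on the wound as separate items: 10.2 already records the consequences of each event and the wound assessment, and 14.6 records the course after treatment.

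The cost is a small edit to the section and the adverse-event form. No visit, treatment or measurement changes. More events may be graded severe than under the present text.
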